### Research teams

The research team will support the government in implementing the interventions assisting the government in resolving the barriers, providing feedback and inputs on performance and optimization processes during co-design workshops, and collecting research data on predefined outcome indicators.

**Central coordinating team (CCT)**: The team will plan and strategize the research activities, ensures the strategic execution in the respective sites. It will also lead the protocol and tool development, establish a relationship with all study sites at district and state level as required, lead the co-development of strategy and implementation plan based on learning from formative research and participatory planning. Quality assurance visits will also be undertaken by the team for monitoring and evaluation of project activities, manage and analyze the data and develop report.

In each study site, the following teams will operate at different levels to orchestrate the conduct of the study which will comprise of:

**Program learning team (PLT):** The team will conduct formative research for implementing the AMB interventions to inform the development of the initial model, undertake continued program learning activities to identify barriers, facilitators and conduct root cause analysis using qualitative research methods. Information on process evaluation indicators will also be collected by the PLT.

**Implementation support team (IST):** The team will handhold the government partners, demonstrate the pragmatic steps of implementation, navigate the barriers, and leverage on the facilitators effectively at facility levels and in the community. This would entail complete and valid documentation of services in the registers/electronic data system to ensure periodic extraction and review of the data. The IST will also facilitate preparedness of the facilities for infrastructure, human resource, training, logistic arrangement including job aid, communication material

**Outcome monitoring team (OMT):** An independent group of researchers will collect quantitative data and monitor the predefined primary and secondary outcomes indicators throughout the implementation phase. Information on the cross-sectional surveys will also be collected by the OMT.

### Study phases

The PRAKASH study will be conducted over a period of 42 months in four sequential phases, each with specific objectives and activities. A gantt chart specifying the timelines of the study phases are presented in Fig 2.

**Fig 2 pone.0351414.g002:**
[figure not shown]
Gantt chart specifying the study timelines.

**Phase I: Preparatory phase (0–3 months)**-The preparatory phase will focus on establishing the groundwork for study implementation. Activities will include stakeholder consultations at state, district, and local levels; hiring and training of study teams; obtaining regulatory and ethical approvals; and pre-testing of data collection tools to ensure contextual relevance and feasibility.

**Phase II: Formative phase and baseline activities (4–9 months)**- This phase will generate evidence on the existing status of anemia management and implementation gaps in the AMB program. Two baseline surveys will be conducted at months 3 and 9 to establish anemia prevalence across six priority beneficiary groups (children 6–59 months and 5–9 years, adolescent girls and boys, pregnant women, and women of reproductive age). Mixed-methods research will assess system-level barriers and facilitators, including service delivery quality, provider knowledge and skills, beneficiary awareness and compliance, procurement systems, and laboratory support. In addition, the formative phase will review the status of AMB interventions such as delayed cord clamping, deworming, fortified rice distribution through social welfare schemes, and SBCC activities related to dietary diversity and anemia prevention.

**Phase III: Implementation phase (10–39 months)**- The implementation phase will operationalize and refine a district-specific intervention model using an iterative and adaptive approach. An initial “Model 0” will be developed through co-design workshops with stakeholders, based on formative research findings. This model will be piloted, refined, and optimized (Models 1, 2, etc.) through continuous cycles of implementation, monitoring, and feedback. Special strategies will be included to reach non-school-going children and women of reproductive age. Cross-sectional surveys will be conducted at months 18, 30 (early implementation and mid implementation survey) and 36 (an end-line survey) to monitor outcome indicators, including anemia prevalence. Process indicators will be tracked through health facilities and sub-centers, complemented by qualitative assessments such as observations, in-depth interviews, and focus group discussions. Data from multiple sources will be triangulated to identify persistent barriers and enablers, with findings continuously fed back to stakeholders for course correction. The optimized implementation model will be concurrently applied across all blocks of the study district with support to government personnel.

**Phase IV: Report preparation and dissemination (40–42 months)**-The final phase will focus on synthesis and dissemination of study findings. Activities will include preparation of comprehensive reports, stakeholder dissemination workshops at district, state, and national levels, and development of a scale-up model adaptable to other sites with necessary contextual modifications.

### Outcome assessment

The outcome monitoring team will conduct five surveys throughout the study. The key indicators to be assessed are categorized in two broad categories:

**1. Impact level Indicator:**
**Primary outcome** will include prevalence of anemia among children 6–59months, adolescent girls (10–19yrs), and women of reproductive age and pregnant women (all trimesters)**Secondary outcomes** would include [1] prevalence of moderate anemia among children 6–59 months, adolescent girls (10–19 yrs), women of reproductive age and pregnant women (all trimesters); [2] prevalence of severe anemia among children 6–59 months, adolescent girls (10–19 yrs), women of reproductive age and pregnant women (all trimesters)
**2. Implementation and Coverage Indicators:**

The implementation strategies covering all 6 domains of interventions will impact on services and coverage outcomes which will be captured as secondary outcomes. The implementation indicators (intervention-wise wise) will include:

### Test, treat, and track individuals with anemia

Proportion of women and childreni. tested for anemia (by group)ii. anemic (mild, moderate, severe) (by group)Proportion of anemic individualsi. initiated on treatmentii. taking treatment for >75% daysiii. who consumed: at least 75% of prescribed dose, 50–75% dose, less than 50% doseiv. with Hb tested every 3 months until resolution of Anemiav. who improved (or recovered) after 3 months of treatmentvi. who did not improve & needed additional tests, received additional testingvii. who were referred to a specialist received a consultation& further treatment

### Prophylactic iron and folic acid supplementation

Proportion of women and children given prophylactic supplements who consumed >75% doses

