The Precision driven Response for Anemia Control and Sustainable Health (PRAKASH) study has been designed to operationalize and test this evidence-based package through a precision-driven, multi-site implementation research study.The study utilizes a theory of change framework that posits for a precision-driven, district-level model that systematically identifies contextual bottlenecks and co-develops tailored implementation strategies (using CFIR determinants linked to ERIC strategies) that are context-specific, scalable, and sustainable with the aim to improve fidelity, reach, and continuity of the six AMB 2.0 pillars. Importantly, it seeks to address well-recognized programmatic challenges including variable Iron Folic Acid (IFA) coverage and adherence, supply chain bottlenecks, limited access to reliable diagnostic tools, and insufficient integration of strategies to tackle non-nutritional causes of anemia through an implementation science approach. By setting a goal of reducing anemia prevalence to below 20%, PRAKASH study aspires to provide a replicable framework that strengthens anemia control efforts and informs national scale-up.

Through this implementation study we aim to co-develop district model of Anemia Mukt Bharat 2.0 which would be optimized to increase coverage and adherence to reduce anemia prevalence to 20% or lower in beneficiary populations (children 6–59 months, adolescent girls (10–19 years), women of reproductive age (20–49 years), pregnant women). The primary objective would be to co-design, optimize, implement and evaluate a model of implementation strategies to deliver the AMB 2.0 interventions across target beneficiaries and reduce prevalence of anemia to ≤20%. The secondary objectives would focus to achieve high and effective population-based coverage (≥80%) of the AMB 2.0 interventions among target beneficiary groups and document the iterative process and implementation outcomes, in developing the optimized model.

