### Anemia-relevant health interventions

Proportion of

i. babies received delayed cord clampingii. LBW infants given prophylactic Iron supplements who consumed>75% dosesiii. Proportion of eligible women and children who received de-worming dosesiv. LBW and Preterm babies screened for anemiav. TB, HIV, malaria patients screened for anemia.

**Eat right to prevent anemia:** Proportion of women and children consumed iron, folic acid, Vitamin B12 rich foods.

**Consumption of fortified rice:** Proportion of households consumed fortified rice.

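### The listed IFA prophylaxis indicator measures adherence among recipients, so it cannot show whether this pillar reached the ≥80% population-based coverage set as a secondary objective

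*Protocol article*

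**What the plan says.** The Introduction of the protocol article sets a secondary objective to "achieve high and effective population-based coverage (≥80%) of the AMB 2.0 interventions among target beneficiary groups". The same section treats reach and adherence as two separate matters: it names "variable Iron Folic Acid (IFA) coverage and adherence" among the known programme problems, and it wants a district model "optimized to increase coverage and adherence to reduce anemia prevalence to 20% or lower".

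Under Outcome assessment, the text on implementation and coverage indicators says that the strategies "will impact on services and coverage outcomes which will be captured as secondary outcomes", and then lists indicators by intervention. For IFA prophylaxis there is one entry: "Proportion of women and children given prophylactic supplements who consumed >75% doses". Under Anemia-relevant health interventions, the item on low-birth-weight infants has the same form: "LBW infants given prophylactic Iron supplements who consumed>75" per cent of doses.

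The treatment indicators under Test, treat, and track report consumption in three bands: "at least 75% of prescribed dose, 50–75% dose, less than 50" per cent.

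**The concern.** The objective concerns a population; the indicator concerns recipients. A person who was eligible but never given supplements belongs in the denominator of population coverage, yet is absent from both numerator and denominator of the listed indicator. If adherence among recipients stays the same, the indicator gives the same reading whether supplements reach a third of eligible people or nearly all of them.

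Reach is one of the problems the study was set up to address. As listed, the IFA pillar has an outcome for whether people take what they are given, but none for whether they are given it. A high reading could be taken as evidence that this pillar met its coverage target when it carries no information on reach.

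**Working it through.** **Step 1: compare the denominators that the article states.**

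| Indicator (Outcome assessment) | Denominator as written | Conditional on having received the service? |
|---|---|---|
| Anemia testing, reported by group | Women and children | No |
| Treatment started; treatment taken | Anemic individuals | No; starting treatment is its own item |
| Deworming | Eligible women and children | No |
| Fortified rice | Households | No |
| IFA prophylaxis | Women and children given supplements | Yes |
| LBW infant iron | LBW infants given supplements | Yes |

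Among these items, only the two on iron prophylaxis are conditioned on receipt. The article uses unconditional denominators elsewhere in the same list.

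**Step 2: relate the indicator to the objective.** Let *r* be the share of eligible people given supplements and *a* the share of recipients who consumed the required doses. The listed indicator is *a*. Effective population coverage is *r × a*.

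**Step 3: put numbers in.** The only input from the document is the 80% target. It states neither *r* nor *a*, so the values below are assumptions chosen to show the range.

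With *a* = 85%, the indicator reads 85% in every row:

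| Receipt *r* | Effective coverage *r × a* |
|---|---|
| 50% | 0.50 × 0.85 = 42.5% |
| 70% | 0.70 × 0.85 = 59.5% |
| 90% | 0.90 × 0.85 = 76.5% |

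Receipt needed for effective coverage of 80% is 0.80 / *a*:

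- *a* = 80%: 0.80 / 0.80 = 100%
- *a* = 85%: 0.80 / 0.85 = 94.1%
- *a* = 90%: 0.80 / 0.90 = 88.9%
- *a* = 100%: 0.80 / 1.00 = 80%

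An indicator reading of exactly 80% is therefore compatible with any effective coverage up to 80%, and equals it only if every eligible person received supplements.

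The plan has no figure of its own to reproduce here: 80% is a target, not a derived number.

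**Step 4: check the adherence bands.** In the treatment indicator, the top band includes exactly 75% and the middle band runs up to 75%, so a person at exactly 75% falls in both. The two prophylaxis items use strictly more than 75%. Treatment and prophylaxis need not share a cut, but the overlap within one indicator is an error of definition.

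**The case against.** The strongest reply is that no rule in the article ties the IFA indicator to the 80% target. The objective covers a six-pillar package, and several other listed indicators are not conditional on receipt. The indicator list is introduced as what will be included, and Supplementary Table 3, which is not at hand, details indicators that the Implementation Support Team takes from service records. IFA distribution may be among them.

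This stands as a limit on the consequence. It does not remove the mismatch. The article presents this list as the place where coverage outcomes are captured, and it fixes the denominator for this pillar. Supplementary Table 3 is described under process indicators, whereas the outcome surveys belong to the independent Outcome Monitoring Team. Distribution counts from records would not by themselves give population-based effective coverage.

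The wording might also be loose and intend all women and children as denominator. The parallel LBW item makes the conditional reading the natural one, and the sentence would need correcting in either case.

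A reader might infer more than the text supports:

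- That the target will be declared met on this indicator. No such rule is stated.
- That most eligible people would be uncovered. At 85% adherence this needs receipt below 0.50 / 0.85 = 58.8%, and the article gives no receipt figure.
- That 80% must be reached in each group separately. The objective does not say so.
- That the indicator falls as reach improves. This needs newly reached people to adhere less well, on which the article is silent.
- That the surveys already sample every eligible person. The Sampling strategy draws several groups from health-worker line lists that it acknowledges are incomplete, and others from neighbouring households.

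**Conclusion.** The point holds for one pillar and one LBW sub-item. The listed indicators measure adherence among recipients and cannot show whether iron prophylaxis reached 80% of the population. The gap between the indicator and effective coverage is *a* × (1 − *r*). At an assumed *a* of 85%, that is 42.5, 25.5 or 8.5 percentage points when receipt is 50%, 70% or 90%. The identity needs no assumption; the sizes rest on assumed receipt and adherence.

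A false claim of success is a risk and not a planned decision. The matter concerns a secondary objective and leaves the primary outcome, anemia prevalence, untouched. It should be corrected before the coverage results are analysed. The overlap at 75% is minor and adds no weight to the denominator point.

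**What to change.** 1. For IFA prophylaxis, define the survey coverage outcome in each beneficiary group as the number who received supplements and consumed the stated share of doses, divided by all eligible beneficiaries surveyed in that group. State that the 80% target for this pillar is judged on it.
2. Report its two components alongside: receipt among all eligible respondents, and adherence among recipients. The present indicator is kept as the second of these.
3. State that the estimate applies to the surveyed frame. The health workers who keep the line lists also ensure IFA distribution, so people they miss may be absent from the sample as well, and the new denominator does not repair that.
4. For LBW infants, use all LBW infants identified in the data source as denominator where that source allows it, and name the source. The Sampling strategy defines no LBW stratum, and the youngest surveyed group starts at 6 months.
5. Make the consumption bands in the treatment indicator mutually exclusive and reconcile them with the cut used in the two prophylaxis items.

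The cost is small: a redefinition, plus making sure that receipt is asked of every eligible respondent and not only of those already known to have supplements. The sample size need not change for this. The downside is a lower reported coverage figure wherever receipt is incomplete.

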### Anemia-relevant health interventions

Proportion of

i. babies received delayed cord clampingii. LBW infants given prophylactic Iron supplements who consumed>75% dosesiii. Proportion of eligible women and children who received de-worming dosesiv. LBW and Preterm babies screened for anemiav. TB, HIV, malaria patients screened for anemia.

**Eat right to prevent anemia:** Proportion of women and children consumed iron, folic acid, Vitamin B12 rich foods.

**Consumption of fortified rice:** Proportion of households consumed fortified rice.

**Jan Andolan for anemia control through behaviour change:**

i. Proportion of beneficiaries involved in community discussions on anemiaii. Dietary practices (consumption frequency of iron rich foods)iii. Awareness levels for anemia control among the beneficiaries
**3. Process Indicators**

The Implementation Support Team (IST) will focus on quantitative data collection, utilizing sources such as Health Management Information System (HMIS), health facility records, records of community health workers, Anganwadi workers and schools/Rashtriya Bal Swasthya Karyakram/Rashtriya Kishore Swasthya Karyakram etc. A detailed list of the indicators to be collected by the IST has been provided in Supplementary Table 3. In parallel, the Program Learning Team (PLT) will gather qualitative insights to investigate the reasons for compliance or non-compliance (for >75% dose, anemia testing among those with chronic/acute infection, delayed cord clamping, to management algorithms), inability to screening, conducting or not conducting SBCC and reasons for use/non- use of IEC materials developed by the responsible stakeholders, underlying reasons for good/poor adherence to AMB algorithms as recommended simultaneously providing with recommendations and valuable feedback to refine outreach efforts.

The PLT will also provide updates on the percentage of sessions observed to assess whether anemia diagnostic tools are used as recommended. The percentage of stakeholders demonstrating adequate knowledge, positive attitudes and appropriate practices will also be collected by the PLT.

Information on implementation- and process-specific indicators such as adherence to defined intervention protocols, documentation of iterative adaptations undertaken during the course of implementation, and systematic recording of key delivery processes would also be captured.

### Data quality and management

Data will be collected in electronic data capture forms (eCRFs) through the REDCap online software. The eCRFs will have an in-built range and logical checks. Data quality will be frequently checked at two levels: at the site by data management team led by site investigators and centrally by the central implementation team (at ICMR).

To ensure study quality,10% of the collected data will be rechecked by the site PI/coordinator and/or the Central Coordinating Unit. Multilevel quality assurance measures will be performed to ensure the correctness, completeness, and timeliness of the data. Each team will ensure the implementation with rigor. They will conduct regular oversight and monitoring of all study activities through regular field visits with joint participation of the Implementation team members. The management and review of the database will be carried out by the team coordinators responsible for their respective areas. The data entry system will incorporate built-in mechanisms for performing range and consistency checks.

### Data analysis

**Quantitative data:** Bivariate analyses will be conducted using chi-square tests for categorical variables and t-tests or non-parametric equivalents for continuous variables to assess associations between outcomes and potential time-varying confounders. To account for clustered data (e.g., individuals nested within facilities and blocks) and potential intra-cluster correlation, analyses will incorporate cluster-adjusted methods. Implementation indicators, including testing, treatment, and tracking of anemia cases; prophylactic iron and folic acid supplementation; anemia-related health interventions; dietary practices (Eat Right initiatives); consumption of fortified rice; and community-based initiatives (Jan Andolan for anemia control) will be summarized using proportions and assessed over time. Pre–post intervention comparisons will be conducted using McNemar’s test for paired categorical outcomes and paired t-test or Wilcoxon signed-rank test for continuous outcomes. Trends across time will be evaluated to compare pre- and post-intervention phases. A p-value < 0.05 will be considered statistically significant. Time series plots will be examined to visualize underlying trends, seasonal patterns, and potential outliers. Multilevel interrupted time series (segmented regression) or mixed-effects regression models will be used as appropriate. SPSS software version 22 will be used for analyzing the quantitative data collected [39]

**Qualitative data:** The interviews will be audio-recorded. Transcriptions will be prepared from the audio recordings and field notes. The NVivo software package will be used to analyze the data, which will be done simultaneously with data collection. Responses will be coded. The codes on the same theme will be grouped into themes and sub-themes. The findings will be weighted by identifying the key themes and estimating the number of times the theme appears and the number of respondents who mentioned the theme. A framework analysis will be used, primarily a case and theme-based analysis. A matrix will display the information and enable us to examine information across rows, which will help maintain the context, and down the columns, which will help in theme development. The collected data will be analyzed through NVivo version 15 software [40].

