**Methods:**

This multi-site study targets six key population groups: children (aged 6–59 months and 5–9 years), adolescents boys and girls (10–19 years), women of reproductive age (20–49 years) and pregnant women. Interventions are anchored in six pillar i. Test–Treat-Track until resolution, ii. prophylactic iron and folic acid supplementation, ensuring high complianceiii. anemia-relevant health interventions, iv. fortified rice distribution, v. dietary diversification and promotion of iron-rich foods, and vi. behavior change communication through Jan Andolan. Anemia prevalence will be estimated through a series of community-based cross-sectional surveys. Mixed methods approach will be employed to assess barriers and enablers at the individual, household, facility, and community levels. The study will utilize implementation science frameworks, including Consolidated Framework for Implementation Research (CFIR) and Expert Recommendations for Implementing Change (ERIC), to guide iterative implementation, real-time model refinement, and monitoring of performance. Information on outcome indicators will be collected to evaluate anemia prevalence, fidelity, feasibility, and service delivery improvements.

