## Methodology

### Study design and setting

The implementation research study will employ a mixed method approach (qualitative and quantitative) for model optimization and interrupted time-series measurements for the outcome evaluation. The six beneficiary groups currently under AMB program: i. Children (6–59 months), ii. Children (5–9 years) iii. Adolescent girls (10–19 years), iv. Adolescent boys (10–19 years) v. women of reproductive age (20–49 years), vi. pregnant women will be included in the study.

Formative research will be undertaken at the individual, community and facility level to identify barriers and facilitators for anemia management implementation across the six selected districts (Table 1). A series of total five cross sectional surveys (consisting of 2 baseline survey, an early implementation, mid implementation and an end-line survey) will be conducted to understand the factors affecting the implementation of the AMB 2.0 program at the individual, facility and community levels and the effectiveness of the implementation program. A thorough evaluation of the healthcare facilities and associated health care workers in the district will also be done to identify gaps that need to be addressed for effective implementation.

**Table 1 pone.0351414.t001:** Details of the study districts.

Sites	Anemia Prevalence as per NFHS-5	Geographical Area (Rural to Urban Ratio)
Site 1 Palghar, Maharashtra	Children 6–59 months: 70.3% Women 15–19 years: 52.1% Non pregnant women 15–49 years: 57.2% Pregnant women 15–49 yrs: 48.5%	52%:48%
Site 2 Koppal, Karnataka	Children 6–59 months: 68.1% Women 15–19 years: 45.6% Non pregnant women 15–49 years: 45.7% Pregnant women 15–49 yrs: 43.3%	79%:21%
Site 3 Palwal, Haryana	Children 6–59 months: 71.6% Women 15–19 years: 59.7% Non pregnant women 15–49 years: 57.2% Pregnant women 15–49 yrs: 56.8%	77%:23%
Site 4 Kendujhar, Odisha	Children 6–59 months: 46.6% Women 15–19 years: 68.2% Non pregnant women 15–49 years: 69% Pregnant women 15–49 yrs: 74.7%	86%:14%
Site 5 Sehore, Madhya Pradesh	Children 6–59 months: 82.4% Women 15–19 years: 50.5% Non pregnant women 15–49 years: 44.8% Pregnant women 15–49 yrs: 58.8%	81%:19%
Site 6 Medchal Malkajgiri District., Telangana	Children 6–59 months: 73.8% Women 15–19 years: 56.1% Non pregnant women 15–49 years: 57.4% Pregnant women 15–49 yrs:53.2%	9%:91%

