### Sampling strategy

For sampling purpose, the universe of study would be the entire district. For every cross-sectional survey, four blocks will be covered from the total number of administrative blocks within the district. Village/ward will be the primary sampling unit. Multi stage cluster sampling will be employed. In each selected village/ward, line list of beneficiaries (children, pregnant women, unmarried WRA (where available) and adolescents’ girls) will be collected from ASHA/ANMs/AWWs. It is recognized that the line listing will not have 100% coverage, but as a part of implementation research study, this aspect will be strengthened as interventions are rolled out. Beneficiaries will be selected randomly from the list. For the remaining groups, where ready line listing may not be available, the next 1–2 households where beneficiary was found using line listing, will be used to identify the rest of the beneficiary groups (children 5–9 years; adolescent boys; WRA & adolescent girls (incase CHWs do not have readily available list for WRA) in the stated order of priority. The sample will include a total of 50 beneficiaries from each village/ ward. The method of sampling would be the same in each of the five survey rounds.

**Sample size calculation:** It is assumed that the prevalence of anemia at baseline will be between 40–60% among different age groups as per NFHS-5 & Comprehensive National Nutrition Survey data. Assuming 20% prevalence of anemia at the end-line with 30% relative precision, 95% confidence interval, 1.45 design effect and assuming different non-response rate (40% for children 6–59 months and 5–9 years, 30% for adolescent girls and boys, 20% for women of reproductive age and 20% for pregnant women), the final sample size is calculated as 400 each for children 6–59 months and children 5–9 years, 350 each for adolescent girls and boys, 300 each for women for reproductive age group and pregnant women for each survey rounds. The focus of the study is on all the 6 groups; however, the four groups (children 6–59 months, adolescent girls (10–19 years), women of reproductive age (20–49 years), pregnant women) are selected for the evaluation of impact indicators. For the remaining two groups (children 5–9 y and adolescent boys), the focus is on the process and coverage indicators.

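### Pre–post comparisons are assigned to paired tests, but the survey rounds that supply prevalence and coverage contain no linked individuals to pair

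*Protocol article*

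**What the plan says.** On testing, the quantitative part of the Data analysis section of the protocol article says: "Pre–post intervention comparisons will be conducted using McNemar’s test for paired categorical outcomes and paired t-test or Wilcoxon signed-rank test for continuous outcomes". It follows directly on the sentence that lists the implementation indicators to be summarized and assessed over time. No linked data set is named, and no separate test is given for comparing unlinked rounds. The threshold is also fixed: "A p-value < 0.05 will be considered statistically significant".

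On the data, the article says:
- Abstract, Methods: "Anemia prevalence will be estimated through a series of community-based cross-sectional surveys".
- Study design and setting: "A series of total five cross sectional surveys (consisting of 2 baseline survey, an early implementation, mid implementation and an end-line survey".
- Sampling strategy: "Beneficiaries will be selected randomly from the list". Groups without a ready list are found in the next one or two households. "The method of sampling would be the same in each of the five survey rounds".
- Study phases: the baseline surveys are at months 3 and 9. For the rest, "Cross-sectional surveys will be conducted at months 18, 30 (early implementation and mid implementation survey) and 36 (an end-line survey".
- Outcome assessment: "The outcome monitoring team will conduct five surveys throughout the study". The impact indicators and the implementation and coverage indicators are listed under that statement.

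Other parts of the analysis do suit this design. Study design and setting names interrupted time-series measurement for the outcome evaluation. Data analysis adds multilevel segmented regression or mixed-effects models, as appropriate, and promises cluster-adjusted methods in general terms.

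**The concern.** McNemar's test uses only discordant pairs: units that changed state in one direction or the other. The paired t and signed-rank tests use within-unit differences. In repeated cross-sections without linkage, neither quantity exists. An analyst who follows the sentence for survey prevalence or coverage would have to line up unrelated respondents, or restrict the test to people who happen to be sampled twice and can be identified. Arbitrary matching gives a p-value without meaning; chance re-sampling gives a small, selected subset.

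At stake are the significance statements attached to simple before–after changes in prevalence and coverage. The article intends such results to inform state action plans and national scale-up.

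**Working it through.** **1. Do pairs exist?** The pre-intervention rounds are at months 3 and 9, and the later rounds at months 18, 30 and 36. That gives 2 × 3 = 6 possible pre–post contrasts, with gaps of 9 months (9 to 18) to 33 months (3 to 36). In every round, respondents are chosen from a line list or from nearby households. Nothing in the article describes a panel, re-contact of earlier respondents or linkage of records across rounds.

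**2. Does the sample size assume pairs?** No. Sampling strategy sizes each round as a single-proportion estimate: 20% prevalence, 30% relative precision (d = 0.30 × 0.20 = 0.06), 95% confidence and a design effect of 1.45.

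- n = 1.96² × 0.20 × 0.80 / 0.06² = 170.7
- 170.7 × 1.45 = 247.6
- Divided by (1 − non-response): 247.6/0.6 = 413 (stated 400), 247.6/0.7 = 354 (stated 350), 247.6/0.8 = 310 (stated 300)

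The stated sizes are close to these, slightly rounded down. The calculation contains no discordance rate or within-person correlation, which agrees with rounds treated as separate samples.

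**3. Could the same people stay in their groups?** Only partly. Over 33 months, a child aged 6–59 months becomes 39–92 months old, so only children aged 26 months or less at month 3 are still in the group (59 − 33 = 26). Over the shortest gap, 9 months, children up to 50 months remain (59 − 9 = 50). No woman is in the same pregnancy 33 months later. These figures show that pairing is not what the design aims at. They do not show that it is impossible for every child or every contrast.

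**4. What happens if rows are paired anyway?** Assume 240 respondents in each of two rounds (for example 400 × 0.6), with 96 anemic (40%) in one and 76 (31.7%) in the other.

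- McNemar: z = (b − c)/√(b + c), where b and c are the two discordant counts. The margins fix b − c at 96 − 76 = 20. The sum b + c depends only on how rows are matched.
- In 10,000 random pairings of these same data, p ran from 0.031 (b + c = 86, z = 20/√86 = 2.16) to 0.086 (b + c = 136, z = 20/√136 = 1.71).
- Unpaired test: pooled p = 172/480 = 0.358, SE = √(2 × 0.358 × 0.642/240) = 0.0438, z = 0.0833/0.0438 = 1.90, p = 0.057.
- Unpaired with design effect 1.45: z = 1.90/√1.45 = 1.58, p = 0.114.

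The same data fall on either side of 0.05 according to an arbitrary row order.

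**5. Does an unpaired comparison need more data?** The net effective size per round is 240/1.45 = 166 (or 245/1.45 = 169 for adolescents). Two-sided at 0.05, power is about 98% for 40% against 20%, and above 99.9% for 60% against 20%. The 40–60% baseline and the 20% end-line are the article's own assumptions.

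**The case against.** The strongest reply is that the sentence can be read narrowly. It ties McNemar's test to paired categorical outcomes, and the programme does generate repeated measurements: quarterly follow-up of treated people, hemoglobin every three months until resolution, and possibly facility records. For those data the tests can be suitable, and this part of the reply stands. But the sentence governs pre–post intervention comparisons without restriction, comes straight after indicators that the surveys supply, and offers nothing for unlinked rounds. Hemoglobin before and after treatment in one person is also a different contrast from before and after the intervention phase.

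It may also be said that the statistical analysis plan could settle this. It could, but it would have to contradict a method that the article states.

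Four stronger readings are tempting, and the document does not support them:
- *That the primary evaluation is invalid.* The article names interrupted time series for the outcome evaluation and adds segmented or mixed-effects models. Nothing makes McNemar's test the test of the primary outcome.
- *That type I error is inflated by clustering.* Data analysis promises cluster-adjusted methods. Nor is this a result of pairing: in simulation with a design effect of 1.45, arbitrarily paired McNemar and the ordinary unpaired test, both unadjusted, rejected equally often (about 10% each).
- *That children and pregnant women can never be paired.* Step 3 shows that some children remain eligible even over the longest gap.
- *That each round draws new villages, so that the samples are fully independent.* The article says that the sampling method is the same each round, not that villages are redrawn, and some respondents are found through neighboring households. Overlapping villages would create correlation between clusters, not pairs of individuals.

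**Conclusion.** The concern holds in a limited form. As written, paired tests are assigned to pre–post comparisons whose survey data contain no pairs, so for survey prevalence and coverage they cannot be carried out meaningfully. The error is confined to those named tests; the time-series and mixed-effects models are unaffected.

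Its size is best described as arbitrariness: a p-value between 0.031 and 0.086 from one pair of samples in the illustration. That range depends on the assumed 240 respondents per round and the assumed 40% and 31.7%, and is not a forecast for this study. A fall as large as the one targeted would be detected with high power by an unpaired test, so the practical risk lies mainly in smaller changes and in coverage indicators.

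The conclusion rests on the article describing no linkage of individuals between rounds. If the full protocol does link respondents, that should be stated and the tests tied to the linked subset.

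**What to change.** Replace the sentence in Data analysis with text such as:

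> Pre–post differences between survey rounds will be estimated as unpaired differences, using cluster-adjusted models with survey round as a factor and village/ward as the cluster (binomial or modified Poisson, or a Rao–Scott test, for categorical outcomes; a linear mixed or design-based linear model for continuous outcomes). Paired tests will be used only for measurements linked within the same individual or facility, such as hemoglobin before and after treatment in tracked anemic persons.

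Village/ward is named because Sampling strategy makes it the primary sampling unit. If the same villages are kept across rounds, the model should allow for the village-level correlation between rounds.

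The cost is a change of wording. It needs no new data, no change to the surveys and no larger sample.
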